### Interventions

Table 2 provides an overview of the three research groups, intervention details and necessary time.

**Table 2 Tab2:**
[figure not shown]
Cluster randomisation / Interventions

Note: *p* participants; *AUAC* Amsterdam University of Applied Sciences

#### Control group

In the control program, participants follow their regular weekly exercise routine without any additional intervention.

#### VITA and VITA-PRO group

Participants engage into their weekly exercise groups, and additionally they will train at least twice a week at home. This results in physical activity for three or more times a week, in order to meet the frequency of training required for effectiveness.

#### Functional exercise training

The home-based personalised exercise training program (VITAMIN-program) is a functional training program with an additional general physical activity plan. The functional exercises focus on daily activities such as climbing stairs, getting out of a chair and lifting groceries that are meaningful for participants and especially designed to improve physical performance. This VITAMIN-program is developed by the AUAS based on the Functional Training for older adults by TNO Research (The Netherlands), expertise on physiotherapy and exercise therapy, expertise on exercise training for elderly and focus group discussions with older adults and their trainers [23]. Participants formulate their own goals to get them motivated to exercise with their personalised program.

Furthermore, the recommendations for physical activity will be incorporated [24]: Physical activity > 5 days a week (at least 3), accumulate at least 30 or up to 60 min in bouts of at least 10 min each to total 150–300 min/wk., at least 20–30 min/day, on a scale of 0 to 10 for level of physical exertion, between moderate- (5–6) and vigorous- (7–8) intensity, at least 2 days a week resistance and flexibility exercises, balance exercise for individuals with mobility problems.

#### Digital support

The VITAMIN-program is supported by an application that runs on a tablet computer, designed by the AUAS and contains content to safely carry out the exercises at home. The insights from the focus group study [23] are taken into account in the user centred approach for the application development and the expertise on persuasive technology and applied psychology is used to develop the application.

#### App design and functions

The application has 5 interfaces with different functions.Today: today’s program of personal exercises with video instructions and alterations of the exercises. After the exercise the participants ranks the exercise on intensity, difficulty and pleasantness.Week planning; overview of the exercise training program for a week.Exercises: an interface containing all exercises in the 18 categories of activities of daily living. Instructions and information about every exercise including safety aspects, necessary equipment and exercise purposes are present.Coach: communication options to contact the coach (Skype, email or call).Profile: A ‘wizard’ to help participants set their own program by their personal goals.

#### Dietary protein counselling

In the VITA-Pro group participants will additionally receive dietary counselling to improve their protein intake. A supervised nutritionist coaches the participant to ingest the optimal amount (1.2–1.5 g per kg body weight per day), timing (breakfast, lunch, dinner, snacks) and source of protein (high quality protein sources, e.g. dairy protein) to improve body composition and physical performance [25–27]. Participants will be advised to consume food products available in food stores that are per definition considered safe. No protein supplements will be used.

#### Coaching

The coaches will contact the participants on a weekly basis in the first 2 months for both the exercise and dietary intervention. Coaching intensity will be tailored to individual needs and will decrease over time. All counselling and coaching instructions are based on the coaching manuals, developed for the VITAMIN project.

#### Handling and storage of data and documents

Data will be collected through: 1) medical and demographical data (e.g., socio-demographic characteristics, current medicine and medical history); 2) home-assessments (e.g., diaries); 3) measurement visits (including anthropometry, cognitive function and physical performance); 4) coaching registration (reports of intervention contacts; 5) tablet data (online storage of exercise behaviour data of participants). During the assessments paper Case Report Forms (CRFs) are used as source documents. Afterwards all data is handled into online-data system Research Manager (Cloud9 Health Solutions) by double data-entry. This allows secure confidential data, protection and privacy of participants. All paper CRFs and electronic CRFs will be coded and therefore privacy of the participants will be protected. Data from the tablet computer of intervention groups is stored on an Internet server in agreement with research regulations.

### Assessments

Table 3 provides a detailed overview of the primary and secondary outcomes as well as explorative outcomes at each time point.

**Table 3 Tab3:** Summary of outcome measures during study visits

	Screening V1	Baseline (T0) V2	6 months (T6) V3	12 months (T12) V4
Physical performance measurements				
Modified Physical Performance Test (M-PPT) [28]		X	X	X
6 Minute Walk Test (6MWT) [33]		X	X	X
Timed Up and Go Test (TUG) [34]		X	X	X
Short Physical Performance Battery (SPPB) [36]		X	X	X
Accelerometry with activity diary		X	X	X
Hand Grip Strength (HGS) [37]		X	X	X
Cognitive performance measurements				
Trail Making, Stroop Color Word test, Letter Fluency [38]		X	X	X
Questionnaires				
Physical Activity Readiness Questionnaire (PAR-Q) [21]	X			
Mini-Mental State Examination (MMSE) [22]	X			
3 day food record [39]		X	X	X
RAND-36 item Health Survey (SF-36) [40]		X	X	X
Geriatric Depression Scale (GDS) [41]		X	X	X
Behavioural Regulation In Exercise Questionnaire (BREQ-2) [42]		X	X	X
Body Composition				
Dual-energy X-ray absorptiometry (DXA) [45, 47]		X	X	X
Air displacement plethysmography (ADP) BodPod [44]		X	X	X
Bioelectrical impedance analysis (BIA) [48]		X	X	X
Mid upper arm muscle circumference (MUAMC) [51, 52]		X	X	X
Height / Weight / BMI [51]		X		
Explorative outcome measures				
Medical and demographical data	X	X	X	X
Tablet usage and satisfaction		X	X	X
Compliance			X	X
Sustainability				X

Note: T0 = post-randomisation baseline visit (V2), T1 = 6 months outcome visit (V3), T2 = 12 month follow-up visit (V4). *BMI* Body Mass Index

X: data will be obtained

#### Primary outcome

The primary outcome is the change in physical performance measured with the Modified Physical Performance Test (M-PPT), between baseline and 6 months [28, 29]. The M-PPT will be performed as an assessment of multiple dimensions of physical function (basic and complex activities of daily living) with different levels of difficulty. The test is well-known in elderly research [30, 31]. The test consists of 9 items [28, 32]; 1. Book lift; 2. Put on and take off a coat; 3. Pick up a coin; 4. Chair rise; 5. Turn 360°; 6. 15.2 m walk; 7. One flight of stairs; 8. Four flights of stairs; 9. Progressive Romberg test. The maximum score is 36; 4 points per item. The test takes approximately 10 to 15 min.

#### All other assessment methods

##### Physical performance tests

*6 Minute Walk Test (6 MWT).* The 6 MWT will be used as a performance-based measure and is often used for populations of healthy older adults [33]. The 6 MWT measures the distance an individual is able to walk over a total of 6 min on a hard, flat surface.

*Timed Up and Go-test (TUG test).* The TUG test will be performed as a measure of physical performance. The TUG test is a well-known test which requires walking speed, strength and balance and is often used in a frail elderly population [34, 35].

*Short physical performance battery (SPPB).* The SPPB will be performed to assess lower extremity function using measures of gait speed, standing balance, and lower extremity strength [36]. A summary performance score of 0 to 12 will be calculated by summing the scores of the tests.

*Accelerometry with activity diary.* Physical activity will be estimated with a 2 dimensional accelerometer (PAM; PE320 Digital Pedometer, Oregon Scientific, USA) and a 3-day record. Participants are requested to wear the accelerometer for 3 days (2 week days and one weekend day) and fill out their major daily physical activities for these 3 days.

*Handgrip strength (HGS).* Three consecutive measures of handgrip strength (kg) at both hands will be recorded using a hand dynamometer (Jamar, USA). The mean and maximum strength effort of the dominant hand will be collected and used as parameters of muscle functioning [37].

##### Cognitive performance tests

*Trail Making Test (TMT).* The TMT is a standardised test to assess a subject’s information processing speed and executive functioning. The score is based on the time needed to complete the test [38].

*The Stroop Color Word Test.* This test is a cognitive task to assess a subject’s information processing speed and executive functioning. The test consists out of three parts. The score is based on the time needed to complete part III [38].

*Letter Fluency Test.* The Letter Fluency test is a cognitive test in which executive function is measured. The participants are asked to generate as many words starting with specific letters within 1 min of time. The score is the total number of the correct words [38].

##### Questionnaires

*3-day food record.* The habitual food intake will be measured using a 3-day food record. This record is designed to estimate the total energy, carbohydrate, fat, protein (including timing and source) as well as micronutrients from foods which are usually consumed [39]. Food intake will be recorded on 2 week days and 1 weekend day.

*RAND-36*. Quality of life will be measured with the RAND-36. The Dutch translation of the 36-Item Short Form Health Survey (SF-36v2) is used. This questionnaire includes a set of generic, coherent, and easily administered quality-of-life measures [40].

*Geriatric Depression Scale (GDS).* This 30-item self-report assessment is used to identify depression in the population of older adults [41].

*Behavioural Regulation In Exercise (BREQ-2) Questionnaire.* This 19-item self-report assessment gains insight into motivation for exercise and regulation in this motivation. The BREQ-2 is the most widely used measure of the continuum of behavioural regulation in exercise psychology research [42].

##### Body composition

*Height, weight and BMI.* Height (m) will be measured and reported to the nearest 0.01 m using a stadiometer. Body weight (kg) will be measured and reported to the nearest 0.1 kg using the calibrated weighing scale of the BodPod without shoes or heavy clothing. Body weight and height are used to calculate BMI (kg/m^2^).

*Air Displacement Plethysmography technology (ADP) - BodPod.* The BodPod (Cosmed, USA) Gold Standard Body Composition Tracking System is an air displacement plethysmograph which uses whole-body densitometry to determine body composition (fat and fat-free mass), and can accommodate a wide range of populations [43, 44].

*Dual Energy X-ray Absorptiometry (DXA).* Body composition will be assessed by DXA. Fat free mass, fat mass and bone mineral density as well as regional measures (appendicular lean and fat mass) will be determined. Appendicular lean mass is a measure of skeletal muscle mass [45]. A DXA scan is a non-invasive procedure with very low radiation dose [46, 47].

*Bioelectrical impedance analysis (BIA).* The Tanita MC-780 MA (2015, Tanita Corporation, Japan) is used to measure Total Body Water (TBW). BIA determines the electrical impedance, or opposition to the flow of an electric current through body tissues which can be used to calculate an estimate of TBW [48]. This BIA is an 8 electrode multi-frequency segmental body composition analyser and besides TBW, visceral fat and muscle mass can be estimated.

*Waist and hip circumference.* Waist an hip circumference will be measured following the World Health Organization (WHO) protocol [49]. With both measures the waist/hip ratio can be derived [50].

*Mid upper arm circumference and triceps skinfold.* A reduction in mid upper arm muscle circumference (MUAMC) is interpreted as a loss of muscle mass. Mid upper arm circumference (MUAC) and the triceps skinfold (TSF) will be measured according to International Society for the Advancement of Kinanthropometry (ISAK) guidelines and with use of adequate equipment [51]. MUAMC and the mid upper arm muscle area (MUAMA) are calculated [52].

##### Explorative outcomes

*Socio-demographic characteristics. (self-report data)* During screening (V1) the participants report in the presence of a study team member: Age, sex, marital status, educational level, ethnicity, exercise group participation, dependency (alcohol consumption and smoking).

*Medical status and history.* Medical history and current status on illness, disabilities and diagnoses is reported by the participant during screening (V1). Also previous and current treatments and/or medications and nutritional supplements are reported. Besides this, information about current specialists or therapists is needed for the eligibility check by the study physician. This is reported in guidance of a study team member. If medical status or medication are changed during the study, this will be reported adequately. (E.g. Adverse Event or Serious Adverse Event).

*Evaluation tablet usage.* At V2 the participant fills out a short questionnaire with questions about earlier experiences with electronical devices. At V3 and V4 the new developed tablet computer behaviour will be assessed by questionnaire. Only intervention groups will receive this.

*Compliance.* Participants will be defined as compliant when ≥80% of the personalised home-based exercise training program is completed during the intervention period. This will be derived from the tablet generated database.

*Sustainability*. The home-based exercise training program will be considered sustainable when at least 80% of the participants in groups VITA and/or VITA-Pro still follow 80% of the training program as planned at baseline after 6 month follow up.

The dietary protein counselling intervention will be considered sustainable when at least 80% of the participants in VITA-Pro still ingest 80% of at least 1.2 g/kg body weight. This is measured at 12 months by evaluation with the coach and previous described measurements.

### Planned statistical analyses

The sample size calculation for the primary outcome parameter is based on the modified Physical Performance Test (M-PPT) of Villareal et al. [29] using the following estimates: Effect size: 1.7 points mean difference in physical performance (M-PPT), a standard deviation (SD) of difference of 1.75, an average cluster size of 10, with an ICC of 2.5. Using the above-mentioned estimates, a significance level (α) of 0.05 and a power of 80%, a sample size of 56 per group is estimated to be sufficient to detect a statistically significant difference in physical performance after 6 months between groups. Assuming 40% drop-out, a total number of 78 subjects is needed per group. Therefore we aim to include 80 subjects per group and in total 240 subjects.

Summary statistics (mean, median, standard deviation, and frequency distribution) will be generated for baseline characteristics. To compare the baseline characteristics between the 3 groups, one-way ANOVA or Kruskal-Wallis test will be used for continuous variables, and Chi-square or Fisher’s exact tests, for categorical variables. Changes in M-PPT, secondary and explorative outcomes will be visualised over the entire time course using mean and standard error of the mean (SEM) per treatment group.

Data will be analysed in accordance with the research questions outlined in the introduction, applying appropriate Linear Mixed Models. Differences within and between treatment groups in the outcome parameter will be analysed. Time, treatment and their interaction will be defined as fixed factors. Subject and group will be included as random factor. If imbalances occur between groups despite randomisation, the baseline values will be treated as covariates.

Detailed analyses will be stated in the Statistical Analysis Plan, which will be finalised before unblinding of the study. All statistical analyses will be performed using SPSS Statistics v22 (IBM, USA). An α of 0.05 will be used to determine statistical significance.

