## Abbreviations

6 MWT: 6 Minute Walk Test
ADL: Activities of daily living
ADP: Air displacement plethysmography
ANAC: Amsterdam Nutritional Assessment Center
AUAS: Amsterdam University of Applied Sciences
BIA: Bioelectrical impedance analysis
BMI: Body mass index
BREQ-2: Behavioural regulation in exercise questionnaire
CRF: Case report form
DXA: Dual-energy X-ray Absorptiometry
GDS: Geriatric depression scale
HGS: Hand grip strength
ICC: Intraclass correlation coefficient
ICH-GCP: International Conference on Harmonisation’s (ICH) Guideline for Good Clinical Practice (GCP)
METC: Medical ethics committee
MMSE: Mini-mental state examination
M-PPT: Modified physical performance test
MUAMA: Mid upper arm muscle area
MUAMC: Mid upper arm muscle circumference
PAM: Physical activity accelerometer
PAR-Q: Physical activity readiness questionnaire
RAND-36: RAND-36 item Health Survey (SF-36)
SD: Standard deviation
SPPB: Short physical performance battery
SPSS: Statistical package for the social sciences
TBW: Total body water
TSF: Triceps skin fold
TUG: Timed up and go test
VITAMIN: VITal AMsterdam older adults IN the city
VUmc: VU University Medical Center
WHO: World Health Organization

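### The sample size is based on an intraclass correlation of 2.5, which is impossible; 0.25 best reproduces the stated 56 per group, and the sponsor should confirm the value used

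*Protocol article*

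**What the plan says.** All the inputs stand in one paragraph of the protocol article, under Planned statistical analyses. The target is a mean difference of 1.7 points on the M-PPT, with "a standard deviation (SD) of difference of 1.75". Clustering enters as "an average cluster size of 10, with an ICC of 2.5". The error rates are "a significance level (α) of 0.05 and a power of 80" per cent. From these the article concludes that "a sample size of 56 per group is estimated to be sufficient". That figure is carried forward: "Assuming 40% drop-out, a total number of 78 subjects is needed per group", and then "we aim to include 80 subjects per group and in total 240 subjects".

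The Abbreviations list has "ICC: Intraclass correlation coefficient", so the symbol has its ordinary meaning. No other ICC value appears in the article.

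**The concern.** An intraclass correlation is at most 1, so 2.5 cannot be the value that was used. In a cluster randomised trial the ICC sets the design effect, and here the choice of value moves the answer from about 21 to about 400 per group. As printed, the reader can derive neither the 56 nor the 80% power.

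The obvious private correction can also mislead. A reader who takes 2.5 as a percentage (0.025) would conclude that 56 is about 2.7 times what is needed (56/21). The later figures of 78, 80 and 240 all start from the 56, so the justification of the whole trial size depends on this input.

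**Working it through.** **Inputs** (Planned statistical analyses): difference d = 1.7; SD = 1.75; average cluster size m = 10; α = 0.05; power 80%. Sidedness is not stated, and two-sided is assumed.

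**Step 1. Size per group without clustering**, two-sample normal formula:

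n = 2 × (1.96 + 0.8416)² × 1.75² / 1.7² = 16.63, rounded up to 17.

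**Step 2. Inflate by the design effect**, DE = 1 + (m − 1) × ICC = 1 + 9 × ICC:

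| Reading of the printed 2.5 | DE | 16.63 × DE | 17 × DE | Fits 56? |
|---|---|---|---|---|
| ICC 2.5, as printed | 23.5 | 390.9 | 399.5 | no |
| ICC 0.25 | 3.25 | 54.1 | 55.25 | yes: 56 from the rounded 17, 55 otherwise |
| ICC 0.025 (2.5%) | 1.225 | 20.4 | 20.8 | no |
| 2.5 is itself the design effect | 2.5 | 41.6 | 42.5 | no |

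Even an ICC of 1, the theoretical maximum, gives DE 10 and 17 × 10 = 170 per group.

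**Step 3. Solve back from 56.** With n = 17, DE = 56/17 = 3.29 and ICC = (3.29 − 1)/9 = 0.255. With n = 16.63, DE = 56/16.63 = 3.37 and ICC = 0.263. Starting from the t-based size instead (17.65, or 18 when rounded up) gives 0.241 or 0.235. The implied ICC is therefore about 0.23 to 0.26 under any of these conventions.

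**Step 4. Power at 56 per group if the ICC is 0.25.** The standard error of the difference is 1.75 × √(2 × 3.25/56) = 0.596, and 1.7/0.596 = 2.85. By the normal approximation, power = Φ(2.85 − 1.96) = 81%, in line with the stated 80%. However, 56 in clusters of 10 is only about 5.6 clusters per arm. With a t reference on about 9 cluster-level degrees of freedom, power is about 72%.

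**The case against.** The existence of the error is not in dispute. The case on the other side concerns how much can be built on it.

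- **The value 0.25 is not proven.** The article does not state sidedness, formula or rounding order. At ICC 0.25 the exact 56 needs n rounded to 17 before inflation; unrounded n gives 55, and t-based versions give 58 or 59. Other routes to 56 exist. ICC 0.025 reaches it if the SD is multiplied by √2 and either power is raised to 90% or α is cut to 0.05/3. A design effect of 2.5 also reaches it, without early rounding, at 90% power (22.27 × 2.5 = 55.7) or at α = 0.05/3 (22.19 × 2.5 = 55.5). All of these change an input that the article prints, so 0.25 remains the best reading. But a reader who infers that 56 can come only from 0.25 goes further than the document allows.
- **The target may be unaffected.** If 0.25 was used, 56 and the figures that follow it do not change because of this error. This stands: the fault would then lie in the reported justification and not in the recruitment target.
- **Further detail is optional.** Power at a lower and a higher ICC, and a note that the ICC refers to the 6-month change, would help a reader. A journal article may leave both to the full protocol or the SAP, and neither is part of the point.

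**Conclusion.** The printed ICC is wrong, and the stated 56 per group does not follow from the stated inputs: literally they give about 391 to 400. Under the usual two-arm normal formula, with two-sided α of 0.05, 80% power, SD 1.75 and clusters of 10, an ICC of 0.25 best reproduces the 56. It does so exactly when n is first rounded to 17. Neither 0.025 (about 21) nor a design effect of 2.5 (about 42 to 43) does.

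Two stronger conclusions are tempting and are not supported:

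- A reader might infer that the trial is short by some 340 participants per group. The 391 to 400 shows only that the printed value cannot have been used; no design could rest on an ICC above 1.
- A reader might infer that moving the decimal point fully restores the 80% power. It does so under the normal approximation (81%); with a small-sample reference for about 5.6 clusters per arm, power is nearer 72%.

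This is nevertheless more than a slip in background text, because the primary sample size and the power statement depend on the figure.

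**What to change.** The sponsor should look up the ICC in the original sample size calculation and correct the sentence. If it was 0.25, print it with its design effect, 1 + (10 − 1) × 0.25 = 3.25, and show that 17 × 3.25 = 55.25 is rounded up to 56. If another value was used, restate the 56 per group and the 80% power to match it, and carry the change through to 78, 80 and 240. The value 0.25 should not be written in on the strength of this back-calculation alone.

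Cost: if 0.25 is confirmed, one number and one line of text, with no change to design, recruitment target or analysis. If it is not, the sample size paragraph has to be reworked.

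### At an ICC of 0.25, 56 evaluable per group in clusters of 10 gives about 72–79% power, not 80%, because the calculation makes no allowance for having only 5–6 clusters per arm

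*Protocol article*

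**What the plan says.** The sample-size paragraph of the protocol article (Planned statistical analyses) takes a mean difference of 1.7 M-PPT points, "a standard deviation (SD) of difference of 1.75", and "an average cluster size of 10, with an ICC of 2.5". With "a significance level (α) of 0.05 and a power of 80"%, it concludes that "a sample size of 56 per group is estimated to be sufficient to detect a statistically significant difference in physical performance after 6 months". It then allows for loss: "Assuming 40% drop-out, a total number of 78 subjects is needed per group". The recruitment target is set in people: "Therefore we aim to include 80 subjects per group and in total 240 subjects".

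Under Study design and setting and under Procedures, existing weekly exercise groups are randomised whole to one of three arms. The planned linear mixed model has time, treatment and their interaction as fixed factors, and subject and group as random factors. The text as shown gives no number of clusters per arm.

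**The concern.** When whole exercise groups are randomised, the treatment comparison is judged against variation between groups. The degrees of freedom then come from the number of clusters, not the number of people. A design effect inflates the variance for clustering, but if the calculation still uses normal quantiles it assumes that the between-cluster variance is known. With five or six clusters per arm it is estimated from few units, and the loss of power is not negligible.

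Two things are at stake. The stated 80% may not be what 56 evaluable people provide. And because the target shown is a count of people, it can be met with different numbers of clusters, although the number of clusters largely determines power at an ICC this high.

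**Working it through.** **Inputs from the document:** difference d = 1.7; SD s = 1.75; average cluster size m = 10; α = 0.05; power 80%; 56 evaluable and 80 recruited per arm; 40% drop-out.

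**Assumptions:** two-sided test; ICC 0.25 (justified in step 1); equal cluster sizes except in step 5.

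**1. Reproducing 56.** Without clustering, the normal-theory size per arm is

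2(1.96 + 0.8416)² × 1.75² / 1.7² = 16.6, rounded up to 17.

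The design effect is DE = 1 + (m − 1) × ICC.

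| ICC | DE | 17 × DE | Gives 56? |
|---|---|---|---|
| 2.5 (as printed) | 23.5 | 399.5 | No |
| 0.25 | 3.25 | 55.25, rounded up to 56 | Yes |
| 0.025 | 1.225 | 20.8 | No |

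So 56 is a normal-theory size times a design effect at ICC 0.25. It contains no allowance for few clusters.

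**2. Power at 56 per arm.** With k = 56/10 = 5.6 clusters per arm:

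- SE = 1.75 × √(2 × 3.25 / 56) = 0.596
- Noncentrality = 1.7 / 0.596 = 2.85
- Normal formula: 81.4%
- Noncentral t, two arms, df = 2(k − 1) = 9.2: 72.1%
- Noncentral t, pooled over three arms, df = 3(k − 1) = 13.8: 75.5%

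**3. Whole clusters of 10 evaluable people.**

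| Clusters per arm | Evaluable per arm | Two-arm df | Pooled df |
|---|---|---|---|
| 5 | 50 | 65.7% | 69.7% |
| 6 | 60 | 75.8% | 78.8% |
| 7 | 70 | 83.3% | 85.4% |

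Both whole-cluster counts next to 5.6 fall short of 80% on either choice of degrees of freedom. Seven clusters reach it.

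**4. The trial as recruited, 80 per arm.**

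*If 10 is the enrolled cluster size*, 80/10 = 8 clusters per arm (two-arm df 14, pooled df 21):

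| Left per arm | Per cluster | DE | Two-arm df | Pooled df |
|---|---|---|---|---|
| 80 (no loss) | 10 | 3.25 | 88.6% | 90.1% |
| 56 | 7 | 2.5 | 85.6% | 87.3% |
| 48 (40% loss) | 6 | 2.25 | 83.9% | 85.7% |

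*If 10 is the evaluable size after loss*, 80 × 0.6 = 48 completers are 4.8 clusters: 63.3% (two-arm df 7.6) or 67.5% (pooled df 11.4).

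**5. Unequal cluster sizes.** The document calls 10 an average and gives no spread. Taking DE = 1 + ((1 + CV²)m − 1) × ICC, with 8 clusters averaging 6 completers and an assumed CV of 0.4, DE = 2.49 and two-arm power is 80.1%. At an assumed CV of 0.6 it is 75.5%.

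**The case against.** **The result depends on an ICC that the document does not print.** This is true. At 56 per arm in clusters of 10, two-arm t power would be 98.5% at ICC 0.025. But at 0.025 the calculation would not have produced 56, so 0.25 is the reading on which the plan's own figure stands. The misprinted ICC is the more basic error in the sentence and must be corrected first. Correcting it to 0.25 does not supply the missing degrees of freedom.

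**The shortfall is small under the planned model.** A three-arm mixed model can pool between-cluster information, and 5.6 clusters cannot exist. Six whole clusters with pooled degrees of freedom give 78.8%. That stands, so the size is given as a range. It remains below 80% throughout, and six clusters of 10 are already 60 people rather than 56.

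**The trial recruits 80 per arm, not 56.** This is the strongest objection, and most of it stands. A reader might infer from the 72% that the trial is underpowered. The document does not support that. Since the eligible members of one exercise group are randomised together, cluster size reads most naturally as the number enrolled, and about 8 clusters per arm keep at least 80% even after 40% loss, if sizes are similar. Only the evaluable-size reading leaves a deficit, and the text does not say which is meant.

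**An article may leave the number of clusters and the analysis details elsewhere.** Fig. 1 and Table 2 are not shown, so it cannot be claimed that no cluster number was ever fixed. The degrees-of-freedom method for the analysis may properly be left to the SAP. Neither changes the sufficiency statement, which the article makes itself.

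**Conclusion.** The point holds for the stated calculation. Reading the ICC as 0.25 and testing two-sided, 56 evaluable per group in clusters of 10 gives about 72% to 75.5% power, or 76–79% if rounded up to six whole clusters, against the 80% stated.

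It does not extend to a finding that the planned 240 subjects are too few. With 8 enrolled clusters of 10 per arm, 40% loss spread within clusters and similar sizes, power is about 84–86%. It falls to about 63–68% only if 10 means evaluable people. Unequal cluster sizes would lower these figures, but the CVs used are assumptions without a source in the document.

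The drop-out allowance is a separate matter: 78 is 56 × 1.4, whereas 56/0.6 is 94.

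**What to change.** In the sample-size paragraph:

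- Correct the ICC and state whether the cluster size of 10 is enrolled or evaluable.
- Restate the calculation in clusters, with t-based degrees of freedom, and drop 56 as sufficient. At ICC 0.25 and with two-arm degrees of freedom, either of these would do: 7 clusters of 10 evaluable per arm (83%), or 8 clusters per arm with at least 6 evaluable each (84%; about 80% at an assumed cluster-size CV of 0.4).
- State the target as at least 8 exercise groups per arm, 24 in total, beside the 80 subjects per arm.

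Of the two options, the second fits the present plan, since 80 recruited with 40% loss leaves 48 = 8 × 6. The first needs 70 completers per arm, which at 40% loss means 70/0.6, about 117 recruited.

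The cost is a rewritten calculation and a cluster-count target. With the second option the number of subjects does not change.

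### Enrolling 80 per group and losing 40% leaves 48 evaluable participants, not the 56 the plan requires; 80 per group covers a 30% loss.

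*Protocol article*

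**What the plan says.** All the relevant statements are in the Protocol article, in the first paragraph of Planned statistical analyses.

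- Requirement before drop-out: "a sample size of 56 per group is estimated to be sufficient to detect a statistically significant difference" between groups in the Modified Physical Performance Test (M-PPT) at 6 months.
- Inputs: a mean difference of 1.7 points, "a standard deviation (SD) of difference of 1.75", and "an average cluster size of 10, with an ICC of 2.5", with α of 0.05 and 80% power.
- Drop-out step: "Assuming 40% drop-out, a total number of 78 subjects is needed per group".
- Enrolment: "Therefore we aim to include 80 subjects per group and in total 240 subjects".

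The Abstract and the section Study design and setting repeat 80 per arm. No other drop-out rate, and no reason for choosing 40%, appears anywhere in the article.

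**The concern.** The 56 is the number judged sufficient for the comparison, and drop-out is added to it afterwards. It is therefore a count of participants with outcome data. Enrolment must then be large enough for 56 to remain after the assumed loss, and 78 is too small for that at 40%.

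At stake is the one sentence that justifies the size of the trial. If it stands, readers will believe that up to 40% of participants could be lost with the required number still in hand. A final report that repeated this would be wrong, and with losses between 30% and 40% the trial would be below its own stated requirement while appearing to be within its allowance.

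**Working it through.** **Inputs, all from Planned statistical analyses:** 56 per group before drop-out; drop-out 40%; 78 per group after drop-out; 80 per group enrolled; difference 1.7; SD 1.75; average cluster size 10; ICC printed as 2.5; α 0.05 (taken as two-sided, since the article does not say); power 80%.

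**Step 1. Where the 56 comes from.** For two means without clustering:

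n = 2 × [1.75 × (1.960 + 0.842) / 1.7]² = 16.6, so 17 per arm.

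The design effect is 1 + (10 − 1) × ICC. An ICC cannot exceed 1, so 2.5 is not usable as printed. Three readings:

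| ICC | Design effect | 17 × design effect |
|---|---|---|
| 2.5 (as printed) | 23.5 | 399.5 |
| 0.25 | 3.25 | 55.25, rounded up to 56 |
| 0.025 | 1.225 | 20.8 |

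Only 0.25 reproduces 56. On that reading clustering is already inside the 56, and the drop-out step stands alone.

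**Step 2. The plan's 78.** 56 × (1 + 0.40) = 78.4, printed as 78.

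**Step 3. The correct inflation.** 56 / (1 − 0.40) = 93.3, so 94 per group and 3 × 94 = 282 in total.

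**Step 4. What the planned enrolment leaves.**

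- 78 × 0.60 = 46.8
- 80 × 0.60 = 48, which is 56 − 48 = 8 short
- Loss that 80 can absorb: 1 − 56/80 = 30%
- Loss that 78 can absorb: 1 − 56/78 = 28.2%

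Steps 2 to 4 do not involve the ICC.

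**Step 5. Power.** SE = 1.75 × √(2 × design effect / n), and normal-approximation power is Φ(1.7/SE − 1.96). The first three rows assume an ICC of 0.25; the last two show the lower reading.

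| Completers per arm | Analysed cluster size | ICC | Design effect | SE | Power (normal) |
|---|---|---|---|---|---|
| 56 | 10 | 0.25 | 3.25 | 0.596 | 81.4% |
| 48 | 10 | 0.25 | 3.25 | 0.644 | 75.2% |
| 48 | 6 | 0.25 | 2.25 | 0.536 | 88.7% |
| 48 | 10 | 0.025 | 1.225 | 0.395 | 99.0% |
| 48 | 6 | 0.025 | 1.125 | 0.379 | 99.4% |

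The third row is eight clusters of 10 per arm, each thinned to 6. A t reference with 16 − 2 = 14 degrees of freedom gives 83.9% there. On the same basis, with the implied 5.6 and 4.8 clusters per arm, the first two rows fall to about 72% and 63%.

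**The case against.** The strongest reply concerns harm. The article randomises existing exercise groups, so individual withdrawals would normally thin those groups and leave their number unchanged. With 80 enrolled in groups of 10, a 40% loss leaves about 6 per group. The design effect then falls to 2.25, and power with 48 completers stays above 80% on either the normal or the t basis. The 75% figure needs whole groups to be lost, or the cluster size of 10 to describe completers, and the article does not say which it means. All these powers also depend on reading the ICC as 0.25; at 0.025 power is about 99%. This stands. It means an underpowered trial is possible but not shown. It also means that 40% loss and 80% power conflict only if the design effect is held at 3.25, as in the plan's own calculation of 56.

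A second reply is that the article shows no formula. A misprinted rate would also explain the figure, since 56/0.72 = 77.8. That stands too: multiplication by 1.40 is the likelier source, but it is an inference. It does not rescue the sentence, because in that case the 40% would be the wrong figure.

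A third reply is that replacing 40% with 30% because 80 happens to support it would alter the investigators' expectation without evidence. This is a fair limit on that form of the correction, and it is reflected in the fix.

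None of these replies touches the count: 60% of 80 is 48 whatever the ICC or the pattern of loss.

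**Conclusion.** The concern holds. The statement that 78 per group suffices at 40% drop-out is wrong: 94 would be needed to keep 56, and the planned 80 keeps 48. The tolerance that 80 per group actually provides is 30%. This follows from the article's own figures and needs no assumption beyond reading 56 as participants with outcome data, which is how the paragraph uses it.

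The effect on power is conditional. With an assumed ICC of 0.25 and a two-sided α, it runs from a fall to about 75% (clusters of 10 analysed, normal approximation) to no loss below 80% (eight clusters of 6, 84% to 89%). With an ICC of 0.025 there is no practical effect. The impossible printed ICC is a separate error in the same paragraph; until it is corrected, no single power figure can be relied on.

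**What to change.** Correct the drop-out sentence in one of two ways, according to what the investigators actually expect.

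1. If a loss of up to 30% is a credible expectation, state that enrolling 80 per group allows for 30% drop-out, because 56/0.70 = 80.
2. If 40% is the honest expectation, keep it, state that 48 per group are then expected to remain, and report the power for the real cluster layout (for example eight clusters per arm with six completers each). Give the ICC used and say whether the average cluster size refers to enrolled or analysed participants.

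The second option is the sounder one if 40% rested on experience, because it does not change the expected loss to suit the enrolment figure.

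The cost is one sentence under the first option, and that sentence plus a short power statement under the second. Enrolment stays at 240, and neither the outcome nor the analysis changes. What is given up is the claim that 40% loss still leaves 56 per group.
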